### Study design

2.1

This trial is a non-inferiority randomized controlled clinical trial, which is designed to compare the clinical efficacy of the Jade moxibustion and traditional moxibustion in treating typical inflammatory pain–KOA. The protocol has been registered on ISRCTN registry (No 21174552) and will be conducted in accordance with the Declaration of Helsinki.

The study flow outline is shown in Figure 1

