### Randomization

2.6

A total of 148 subjects with KOA who are eligible per protocol will be randomly assigned to group A - Jade moxibustion group or group B - traditional moxibustion group in a 1:1 ratio. The subject will first receive a brief phone consultation, after that, the subject will be allocated to the site. After the investigator and the subject signed the informed consent, the investigator will perform a simple rheumatic examination. The investigator will make a diagnosis based on the knee x-ray film brought by the subject or the knee X-ray performed at site. Only the subject who meet the inclusion/exclusion criteria will be randomized by central network randomization program. Then investigator will make baseline assessment and arrange treatment.

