### Sample size

3.5

There is study indicates that at least a 36% increase in WOMAC score is considered effective.^[36]^ In the previous study of the research group, the average effective rate of the Jade moxibustion group was 55.56%, compared with 46.51% in the traditional moxibustion group. Based on the results of our pilot study and previous reports, we used non-inferiority test to calculate the sample size (α = 67 per group) with α = 0.025, 1−β = 80%, and a cutoff of 0.5. In other words, we expect a sample size of 62 subjects per group to be sufficient to detect statistically significant differences between the 2 groups. There were no cases of shedding in the 2 treatment groups in the previous trial. In order to prevent the occurrence of shedding resulting in insufficient sample size (preset 10% shedding rate), we will recruit 74 subjects for each group, and a total of 148 subjects need to be recruited.

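### The sample-size section gives 67 and then 62 per group for one calculation, and presents a non-inferiority calculation as enough to detect a difference, for which power is only about 17–20%

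*Protocol article*

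**What the plan says.** The Study design section (2.1) fixes the objective: "This trial is a non-inferiority randomized controlled clinical trial". Allocation is equal between the two arms (Randomization, 2.6).

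The Sample size section (3.5) then gives:

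- the planning rates: "the average effective rate of the Jade moxibustion group was 55.56%, compared with 46.51% in the traditional moxibustion group";
- the method and first result: "we used non-inferiority test to calculate the sample size (α = 67 per group" (the α before 67 is evidently a slip for n);
- the settings: "with α = 0.025, 1−β = 80%, and a cutoff of 0.5";
- a restatement, offered as equivalent: "we expect a sample size of 62 subjects per group to be sufficient to detect statistically significant differences between the 2 groups";
- a 10% allowance for dropout, after which "we will recruit 74 subjects for each group", 148 in total.

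The Statistical analysis section (3.6) plans a χ² comparison of week-4 remission rates, with the significance level set at 0.05.

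**The concern.** One calculation is reported with two evaluable sample sizes, and nothing in the article reconciles them. The restatement also changes the question. A calculation made to rule out that jade is worse by more than a margin becomes a statement that the trial can detect a difference between the arms. Those are different hypotheses and need very different numbers.

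Two things are at stake. A reader may take 62 completers per group as enough, although recruitment was built on 67. A reader may also believe that the χ² test in section 3.6 is adequately powered. A non-significant result, which is the likely outcome even if jade is truly 9 points better, could then be taken as evidence that the treatments are similar.

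**Working it through.** **Inputs (protocol article, section 3.5 unless noted).** Jade rate 0.5556; traditional rate 0.4651; difference 0.0905; α = 0.025, sidedness not stated and taken as one-sided, as is usual for non-inferiority; power 80%; cutoff 0.5, scale not stated; dropout 10%; equal allocation (2.6). The 0.05 in section 3.6 is taken as two-sided.

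**1. Which figure leads to 74?**

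| Evaluable per group | × 1.1 | ÷ 0.9 |
|---|---|---|
| 67 | 73.7 → 74 | 74.4 → 75 |
| 62 | 68.2 → 69 | 68.9 → 69 |

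The 74 comes from 67 multiplied by 1.1. Neither convention takes 62 to 74.

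**2. Can the stated inputs reproduce 67 or 62?** For a risk-difference margin M,

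n = (z₀.₉₇₅ + z₀.₈₀)² × V / (M + 0.0905)²,

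with V = 0.5556 × 0.4444 + 0.4651 × 0.5349 = 0.2469 + 0.2488 = 0.4957 and (1.960 + 0.842)² = 7.849.

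- M = 0.5: 7.849 × 0.4957 / 0.5905² = 11.2, so 12 per group.
- M = 0.15: 7.849 × 0.4957 / 0.2405² = 67.3, so 67 or 68.
- M = 0.16: 7.849 × 0.4957 / 0.2505² = 62.0.

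On other scales, 0.5 as an odds-ratio margin gives 57, as a risk-ratio margin 21, and as a standardised mean difference 63. The last is close to 62 but makes no use of the quoted rates. So the printed cutoff, read as a risk difference, gives neither figure. The 0.15 and 0.16 are solved backwards from 67 and 62; neither is in the document.

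**3. Power to detect a difference.** With SE = √(0.4957 / n), power ≈ Φ(0.0905 / SE − 1.96). No margin enters.

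| n per group | SE | 0.0905 / SE | Power (unpooled) | Power (pooled null variance) | Exact χ² power |
|---|---|---|---|---|---|
| 62 | 0.0894 | 1.012 | 17.2% | 17.0% | 19.1% |
| 67 | 0.0860 | 1.052 | 18.2% | 18.0% | 17.4% |
| 74 | 0.0818 | 1.106 | 19.6% | 19.4% | 21.6% |

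The exact figures do not rise steadily because the test is discrete. For 80% power, n = 7.849 × 0.4957 / 0.0905² ≈ 475 per group (478 with pooled null variance, 500 with continuity correction). That is more than six times 74.

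**4. Non-inferiority power at 67 per group, under an assumed margin.** Power = Φ((M + true difference) / SE − 1.96). SE is 0.0860 at the quoted rates. If both rates are 46.51%, SE = √(2 × 0.4651 × 0.5349 / 67) = 0.0862.

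| Assumed risk-difference margin | Quoted rates | Both rates 46.51% |
|---|---|---|
| 0.10 | 60% | 21% |
| 0.15 (back-solved from n = 67) | 80% | 41% |
| 0.20 | 92% | 64% |
| 0.50 (printed figure read as a risk difference) | > 99.9% | > 99.9% |

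At 62 per group and a margin of 0.15, power at the quoted rates is 77%.

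**The case against.** The strongest reply is that this is loose wording with no operational effect. The article calls the trial non-inferiority in sections 2.1, 3.5 and 4; the recruitment target is 148 throughout; and 74 per group exceeds both 67 and 62. A non-inferiority trial need not have power for superiority. The risk of misreading a non-significant χ² also comes from the test chosen in section 3.6, which correcting section 3.5 does not change. All of that stands, and it limits the point: neither the design nor the recruitment number is shown to be wrong. It does not rescue the sentence, which states a sample size that conflicts with the one before it and a power that the quoted rates contradict.

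A second reply is that the article alone cannot show that 62 is the mistaken figure. That also stands. Read as a risk difference, the printed cutoff yields neither number. A standardised-mean margin of 0.5 gives 63, and section 3.1 defines the primary outcome as a continuous WOMAC pain change. The document shows only that 74 was built from 67, so the two figures should be reconciled, not one simply struck out.

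A reader might also infer that the margin is really 0.15, and that 67 per group therefore has 80% power at the stated margin and 41% if the arms are equal. The article does not support this. The only printed value is "a cutoff of 0.5"; 0.15 is what makes 67 come out, and the power figures move widely with it, as step 4 shows.

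**Conclusion.** The point holds for what section 3.5 states. Two evaluable targets are given for one calculation, and only 67 is consistent with 74 per group and 148 in total. The claim that the number suffices to detect a significant difference is wrong by a wide margin: about 17–18% power at 62–67 per group and 19–20% at 74 by the usual approximation (17–22% by exact calculation). This rests only on the quoted rates, equal allocation and two-sided 0.05 (one-sided 0.025 is equivalent here), and needs no assumption about the margin.

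The finding does not extend to saying that the trial is too small for its own non-inferiority objective. That cannot be judged until the margin and its scale are confirmed. The sentence should be corrected because the sample size and power are figures that the trial relies on and the correction costs only wording.

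**What to change.** In section 3.5:

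1. Remove the claim of power to detect a difference and state that the trial is not powered for superiority.
2. Give one evaluable target per group. 67 is the figure consistent with 74 and 148; the sponsor should check it against the original calculation and account for the 62.
3. State the non-inferiority margin with its scale, and reconcile it with the printed 0.5, which as a risk difference gives about 12 per group. Correct the symbol before 67.
4. Print non-inferiority power only at the confirmed margin, at the quoted rates and also at equal rates, so that the dependence on the assumed 9-point advantage for jade is visible. The figures for 0.10, 0.15 and 0.20 in step 4 are illustrations and should not be copied in before confirmation.

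Keep recruitment at 148. The cost is a check of the original calculation and a few sentences of wording; the drawback is that the stated claim becomes less favourable.

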### Statistical analysis

3.6

Intention-to-treat analysis is the principle of this study, which includes all subjects in the designated treatment group, as well as subjects who have completed at least one course of treatment. The significant difference level is set to 0.05. The baseline characteristics of subjects will be summarized in both groups. For continuous results, the normal distribution of the data is labeled as the mean (standard deviation). For the main outcome, the remission rate of the fourth week will be calculated and χ^2^ test will be used to compare the Jade moxibustion group with the traditional moxibustion group. For secondary outcomes, unpaired scores including WOMAC pain, functional and stiffness scores, SF-36, expectation and reliability of treatment, and overall treatment outcome will be compared at all follow-up time points in both groups. T-test or Wilcoxon rank sum test will be used to compare continuous variables. We will use SPSS version 22 (IBM SPSS Statistics, NY) for statistical analysis.

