### Primary outcome indicators

3.1

The primary outcome measure is the change in pain relative to baseline at the Western Ontario and McMaster Universities Osteoarthritis Index (WOMAC) in 4 weeks. The most painful knee joint for the subject will be recorded at the baseline, which will be the joint we measured throughout the trial. We will also measure WOMAC pain at week 2, 8, 12, and 24.

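### Section 3.6 tests the main outcome as a two-category remission rate although section 3.1 names the continuous change in WOMAC pain; the cut discards information, and the power lost depends on a margin and SD that the protocol does not give

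*Protocol article*

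**What the plan says.** Section 3.1 states: "The primary outcome measure is the change in pain relative to baseline at the Western Ontario and McMaster Universities Osteoarthritis Index (WOMAC) in 4 weeks". That is a continuous quantity.

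Section 3.6 states: "For the main outcome, the remission rate of the fourth week will be calculated and χ^2^ test will be used to compare" the jade and traditional moxibustion groups. The same section lists the WOMAC pain score among the secondary outcomes and compares continuous variables by t-test or Wilcoxon rank sum test.

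Section 3.6 does not define remission. The only candidate in the document is in section 3.5: "at least a 36% increase in WOMAC score is considered effective". It names no WOMAC subscale.

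Section 3.5 also sizes the trial on response rates: "the average effective rate of the Jade moxibustion group was 55.56%, compared with 46.51% in the traditional moxibustion group". The calculation is for non-inferiority, "with α = 0.025, 1−β = 80%, and a cutoff of 0.5". It gives 67 per group, while the next sentence says "we expect a sample size of 62 subjects per group to be sufficient to detect statistically significant differences between the 2 groups". Recruitment is 74 per group after allowance for dropout.

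**The concern.** The outcome named as primary uses the full scale; the analysis named as main reduces each patient to success or failure. If remission means the 36% rule, a patient who improves by 35% counts the same as one who does not improve at all, and a patient who improves by 37% counts as a full success. The planning rates put the cut near the middle of the distribution.

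The WOMAC pain scores will be collected and compared on the full scale anyway, but only in a supporting role. At stake is the power of the main comparison from the same patients and visits, and whether the headline result addresses the outcome that section 3.1 promises.

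**Working it through.** **Inputs from section 3.5.** p_J = 0.5556, p_T = 0.4651, difference 0.0905; α = 0.025, taken as one-sided; power 80%; n = 67 per arm before dropout (62 also printed).

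**Assumptions, not in the document.** Normally distributed scores with equal SD in both arms; the 36% rule and WOMAC pain change reflect the same underlying variable. No WOMAC SD or mean change is given.

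**1. The plan's own sample size.** n = (1.96 + 0.842)² × [p_J(1−p_J) + p_T(1−p_T)] / (m + 0.0905)², with the bracket equal to 0.2469 + 0.2488 = 0.4957.
- m = 0.5, the printed cutoff read as a rate difference: n = 11.2, so 12 per group. This reproduces neither 67 nor 62.
- m = 0.15: n = 67.3, which matches 67. I therefore use 15 percentage points as an assumed margin. It is not printed anywhere.

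**2. Information kept by the cut.** The efficiency of a two-category cut of a normal score is φ(z)² / [p(1−p)]. At p = 0.4651 this is 0.3974² / 0.2488 = 0.635. At p = 0.51, the middle of the two rates, it is 0.636. So about 64% is kept.

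**3. Implied effect on the full scale.** d = Φ⁻¹(0.5556) − Φ⁻¹(0.4651) = 0.140 + 0.088 = 0.227 SD.

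**4. The χ² difference test as written** (two-sided 0.05, n = 67).
- Binary: standard error √(0.4957/67) = 0.0860; Φ(0.0905/0.0860 − 1.96) = 0.18.
- Full scale: Φ(0.227 × √(67/2) − 1.96) = Φ(1.316 − 1.96) = 0.26.
- Loss: about 8 points. Power is low either way.

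**5. Non-inferiority, assumed 15-point margin, n = 67.**
- Binary: Φ(0.2405/0.0860 − 1.96) = Φ(0.836) = 0.798.
- Equivalent margin on the score: M = Φ⁻¹(0.4651) − Φ⁻¹(0.3151) = −0.088 + 0.481 = 0.394 SD.
- Full scale: Φ[(0.227 + 0.394) × √33.5 − 1.96] = Φ(1.636) = 0.949.
- Loss: about 15 points. For 80% power the requirement is 67.3 per arm binary against 40.7 on the full scale.

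**6. Other percentage-point margins (n = 67, each mapped to SD in the same way).**

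| Margin | Binary | Full scale | Gain |
|---|---|---|---|
| 10 points | 60% | 80% | 20 |
| 15 points | 80% | 95% | 15 |
| 20 points | 92% | 99% | 7 |
| 50 points (as printed) | above 99.9% | – | none possible |

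**7. Other score shapes** (40,000 simulated trials, n = 67, 15-point margin, t-based interval): normal 78.9% against 94.7%; skewed gamma 78.6% against 94.4%; logistic 78.7% against 88.3%; t with 5 df 78.5% against 83.3%. The two heavier-tailed shapes give gains of about 10 and 5 points.

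**8. Margin set directly on the WOMAC scale** (d = 0.227, n = 67): M = 0.39 SD gives about 95%; 0.30 SD about 86%; 0.26 SD about 80%; 0.20 SD about 70%.

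**The case against.** The responder analysis matches the stated basis of the sample size: section 3.5 cites a source for the threshold and uses response rates from the group's earlier study. A responder endpoint is a legitimate choice, and the full-scale comparison is planned as a secondary analysis, so no data go unanalysed. This stands, and it means that the χ² comparison is not invalid because it is binary. It does not explain why section 3.1 names a different, continuous outcome as primary.

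A reader might infer from step 5 that the plan simply loses 15 points of power, or that the change would cut the chance of an inconclusive trial from 20% to 5%. The document does not support either statement. The 15-point margin is inferred from the sample size, normality and equal SD are assumed, and 0.39 SD comes from mapping normal quantiles. A WOMAC-point margin set on clinical grounds need not equal 0.39 SD; step 8 shows that a stricter one shrinks the gain, removes it or reverses it. For the test actually named in section 3.6 the figure is 8 points, and at the printed cutoff of 0.5, read as a rate difference, nothing is lost. That last reading cannot have produced 67 per group, however.

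A reader might also take the information loss as separate from the conflict between sections 3.1 and 3.6. It is not: aligning 3.6 with 3.1 is itself the remedy. The loss would remain only if the sponsor settled the conflict in favour of the responder rate.

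**Conclusion.** The point holds as a conditional improvement that is cheap to make. The main analysis in section 3.6 does not use the continuous outcome that section 3.1 defines, and a cut near 50% keeps about 64% of the information in a normal score.

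The cost in power is about 8 points for the χ² difference test as written (18% against 26% at 67 per arm). It is about 15 points for a non-inferiority comparison (80% against 95%), provided that the margin is 15 percentage points, that scores are normal with equal SD, that the 36% rule and WOMAC pain share one underlying variable, and that the WOMAC margin is equivalent at 0.39 SD. Margins of 10 to 20 points give about 20 to 7 points; heavier tails give about 5 to 10 with a t-test. No single figure can be given unconditionally, because the protocol prints no WOMAC SD and its cutoff does not reproduce its sample size.

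**What to change.** In section 3.6, make the main analysis the between-arm difference in mean change in WOMAC pain from baseline to week 4, as section 3.1 names. Report it with a two-sided 95% confidence interval, and judge that interval against a non-inferiority margin justified in WOMAC points and fixed in advance. Keep the week-4 responder rate, with remission defined and with a risk difference and 95% confidence interval, as a secondary analysis.

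In section 3.5, keep 74 per arm and restate the power for that analysis and margin.

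The cost is rewording of 3.5 and 3.6, with no added patients, visits or measurements. The real work is to obtain an SD and defend a WOMAC-point margin. The group's earlier study is a possible source, but the document does not show that it holds a usable SD. The headline result becomes a mean difference, with the responder rate beside it to help clinical reading.

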## Discussion

4

The purpose of this study is to explore an effective moxibustion replacement therapy, Jade moxibustion for KOA. The trial will evaluate its non-inferior efficacy compared with traditional moxibustion. Subjects will receive 3 times treatment a week. For Chinese medical external treatment, the frequency of 3 times a week is the most common treatment for KOA. One limitation of this trial is that due to different treatment instrument, the operators will know about the group allocation, which may lead to subjects’ bias. Therefore, study may use the expectation scale to measure the attitude of the subject to the treatment. The trail is aimed to provide reliable evidence for Jade moxibustion in the treatment of KOA, and to make up for the lack of clinical efficacy research in this field. Also, to provide reliable data for our future multicenter randomized clinical trial. Traditional moxibustion therapy produces heavy smoke with unpleasant smell. The smoke of moxibustion is considered as a biological hazard to health,^[37]^ which is therefore prohibited from use in many clinics and hospitals. Jade moxibustion is a new therapy based on the theory of TCM and is easy to operate with no smoke, which can be further explored for treatment amount and duration.

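### The trial is declared and sized as non-inferiority, but the primary analysis is a χ² test of equality with no margin or non-inferiority decision rule

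*Protocol article*

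**What the plan says.** All references are to the protocol article.

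- Study design (2.1): "This trial is a non-inferiority randomized controlled clinical trial".
- Discussion (4): "The trial will evaluate its non-inferior efficacy compared with traditional moxibustion".
- Sample size (3.5): "we used non-inferiority test to calculate the sample size", "with α = 0.025, 1−β = 80%, and a cutoff of 0.5". The planning rates are given as "the average effective rate of the Jade moxibustion group was 55.56%, compared with 46.51% in the traditional moxibustion group". The section states 67 per group, then 62 per group (described as enough to detect a significant difference), then 74 per group after a 10% allowance for dropout.
- Statistical analysis (3.6): "The significant difference level is set to 0.05", with sidedness not given. Then: "For the main outcome, the remission rate of the fourth week will be calculated and χ^2^ test will be used to compare" jade with traditional moxibustion. No margin, interval, one-sided test or decision rule follows, and the cutoff in 3.5 is not mentioned again.
- Primary outcome indicators (3.1): the primary outcome is the change from baseline in WOMAC pain at 4 weeks, a continuous measure. Section 3.6 analyses a remission rate.

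**The concern.** The design and the named test have different null hypotheses. Non-inferiority sets out to reject that jade is worse than traditional moxibustion by at least a margin. The χ² test sets out to reject that the two rates are equal. Failing to reject equality leaves open whether a deficit as large as the margin has been excluded.

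The primary conclusion rests on this one sentence. A non-significant result would not support the stated objective, and a significant result in favour of jade is a superiority finding, for which the trial is not sized. Because the article names a specific test, this is not a detail left for a separate analysis plan: a plan that matches the article inherits the problem, and one that departs from it contradicts the article.

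**Working it through.** **Inputs.** From 3.5: jade rate 0.5556, traditional rate 0.4651, α = 0.025 (taken as one-sided), power 80%, cutoff 0.5, and 67, 62 or 74 per group. Assumed: margins M of 0.05 to 0.20 on the risk-difference scale, because the article gives no usable margin.

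**1. The plan's own sample size.**
n per group = [p_J(1−p_J) + p_T(1−p_T)] × (1.960 + 0.842)² / (M + p_J − p_T)²

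The variance sum is 0.2469 + 0.2488 = 0.4957, the squared term is 7.849, and p_J − p_T = 0.0905.

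- M = 0.50: 0.4957 × 7.849 / 0.5905² = 11.2, so 12 per group. This is neither 67 nor 62.
- Other readings of 0.5 at the planning rates: odds-ratio margin 57; risk-ratio margin 21; half the control rate 38; 0.5 SD on a mean 63. The last is close to 62 but is not a calculation on rates. None gives 67.
- As a risk difference, 0.5 exceeds the whole control rate of 0.4651, so a jade response rate of 0% would lie inside it.
- M = 0.05, 0.10, 0.15, 0.20: 198, 108, 68 and 47 per group.

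**2. Two possible results with 67 per group** (uncorrected χ²; Wald 95% interval for jade minus traditional).

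| Jade | Traditional | χ² p | Difference | 95% CI |
|---|---|---|---|---|
| 21/67 | 31/67 | 0.076 | −14.9 points | −31.2 to +1.4 |
| 37/67 | 31/67 | 0.30 | +9.0 points | −7.9 to +25.8 |

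Both are non-significant. The first leaves a 31-point deficit open. The second would meet a margin of 0.10 or 0.15. The χ² p-value does not separate them in the way the objective requires.

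**3. How often a significant χ² favours jade at the planning rates** (exact enumeration of all binomial outcomes, two-sided 0.05).
62 per group: 19%. 67 per group: 17%. 74 per group: 21%. The uneven order comes from the discreteness of the test; the normal approximation gives 17.0%, 18.0% and 19.4%. By the usual formula, 80% power for χ² would need 478 per group.

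**4. χ² against a confidence-interval rule, 67 per group** (exact enumeration; the rule declares non-inferiority if the lower 95% limit is above −M).

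| Assumed M | χ² non-significant when jade is truly worse by M | Interval rule falsely declares non-inferiority | Interval rule succeeds at planning rates |
|---|---|---|---|
| 0.10 | 79% | about 2.5% | 61% |
| 0.15 | 58% | about 2.5% | 79% |
| 0.20 | 32% | about 2.5% | 93% |

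The normal approximation to the last column is Φ[(M + 0.0905)/√(0.4957/67) − 1.960], which gives 60%, 80% and 92%.

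**The case against.** **A significant χ² result in favour of jade would imply non-inferiority.** This stands. A reader might infer that the planned test can never establish non-inferiority; that goes too far. What remains is that this route succeeds in only about 17% to 21% of trials at the planning rates.

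**The article never says that p > 0.05 will be read as non-inferior.** Also true. A reader might infer that it plans this, but no sentence says so. The figures in the second column of the last table show what such a reading would risk. Section 3.6 offers no other rule.

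**The significance levels agree.** A reader might take 0.025 in 3.5 and 0.05 in 3.6 as a contradiction. The document does not support that: one-sided 0.025 and two-sided 0.05 are the same level in each direction, and χ² is non-directional. Only the sidedness is unstated, which calls for clarification.

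**A margin exists.** Section 3.5 does give "and a cutoff of 0.5". It has no scale, does not reproduce 67 or 62 as a risk difference, and is not carried into 3.6. It is tempting to read it as a slip for 0.15, since 0.15 gives 68 per group, but nothing in the article says so and 0.15 is used here only as one value in a range.

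**Conclusion.** The mismatch between objective and test is established from the article's own sections and nothing elsewhere in it supplies a non-inferiority rule. The primary analysis as written does not test the stated hypothesis, and this should be corrected before analysis.

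The direction of the conclusion does not depend on which stated sample size is used or on which of the assumed margins applies. Its size does: the proportion of truly inferior trials with a non-significant χ² falls from 79% to 32% as the assumed margin widens from 0.10 to 0.20. The calculations also assume a control rate of 46.51%, uncorrected Pearson χ², a Wald interval and no missing data.

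**What to change.** 1. Replace the χ² sentence in 3.6: estimate the week-4 difference in remission rate (jade minus traditional) with a two-sided 95% confidence interval, equivalent to the one-sided 0.025 in 3.5. Conclude non-inferiority only if the lower limit lies above minus the margin. Test superiority on the same interval only after non-inferiority is met.
2. Replace the cutoff of 0.5 in 3.5 with a justified margin on a named scale. Without this step, a literal reading would test against a 50-point deficit, which almost any result passes.
3. State that the 0.05 level is two-sided.
4. Name the primary outcome to which the rule applies. If it is the continuous WOMAC pain change in 3.1, the estimate and margin must be on that scale.
5. Restate the power of the planned size under the chosen margin. For the remission rate with 67 per group it is about 80% at 0.15 but about 60% at 0.10.

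**Cost.** Rewording of 3.5 and 3.6, and possibly a less favourable stated power. The change of analysis needs no new data. Whether 74 per group is enough for 80% power depends on the margin: at 0.10 the formula asks for 108 and at 0.05 for 198, so the sponsor would have to accept lower power or revisit the size.

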### Secondary outcome indicators

3.2

The most important secondary outcome measurement is the improvement of WOMAC function in week 4. We will also assess the total score, function score and stiffness score of WOMAC at baseline, weeks 2, 8, 12, and 24. Visual analog scale pain score will be used to evaluate the arthritis pain of subjects at baseline, weeks 2,4, 8, 12, 24. SF-36 will be used to measure the quality of life of the subjects in the 4th, 12th, and 24th week. In addition, we will evaluate the efficacy of a 5-point scale in the fourth week (1 = very poor, 2 = poor, 3 = general, 4 = OK, 5 = very good.).

Any adverse event, whether related to treatment, requires the subject and investigator to report on each treatment or visit. Side effects include redness and blisters by Jade moxibustion and traditional moxibustion. Serious adverse events will be reported to the Ethics Committee. During the follow-up period (week 5 to week 24), we will call the subject weekly to find out about the adverse reactions and side effects that may occur during the week.

After 4 weeks of treatment, investigator will ask the subjects about the safety of the treatment: safe, fewer safe, have safety problem, and have serious safety problem. After each treatment we will ask the subject's feeling: “What do you feel during the treatment? 1. Heat; 2. Cold; 3. Pain; 4. no feeling; 5. Other, please describe”

The subjects will be allowed to take the analgesic or non-steroidal anti-inflammatory drugs used before the test, we will ask subjects to record the daily dose during the entire clinical trial, and then analyze the changes in the dose.

We will measure the outcome of the baseline, week 2, 4, 8, and 12 at the hospital. For the outcome of Week 24, we will mail the questionnaire to the subjects and ask them to post them back after filling them out.

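### Secondary scores are compared by a separate unpaired test at each visit, which ignores each patient's other scores and, unless gaps are filled, cannot include everyone randomised

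*Protocol article*

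**What the plan says.** Statistical analysis (3.6) sets the population: "Intention-to-treat analysis is the principle of this study, which includes all subjects in the designated treatment group". For secondary outcomes it lists unpaired comparisons of WOMAC pain, function and stiffness, SF-36 and other measures, which "will be compared at all follow-up time points in both groups", and names the method: "T-test or Wilcoxon rank sum test will be used to compare continuous variables". The main outcome is handled differently: "the remission rate of the fourth week will be calculated and χ^2^ test will be used".

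The scores are longitudinal. Besides baseline and the week-4 primary time point, Primary outcome indicators (3.1) says "We will also measure WOMAC pain at week 2, 8, 12, and 24". Secondary outcome indicators (3.2) gives VAS pain at baseline and weeks 2, 4, 8, 12 and 24, and SF-36 at weeks 4, 12 and 24. It adds: "For the outcome of Week 24, we will mail the questionnaire to the subjects and ask them to post them back".

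On loss, Sample size (3.5) uses a "preset 10% shedding rate" and reports no losses in the previous trial. Withdrawal criteria (2.5) asks early leavers for a questionnaire survey, without saying what it contains or how it enters the analysis.

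**The concern.** An unpaired t-test or rank sum test at one visit needs a value at that visit. A patient with a week-2 score and no week-4 score contributes nothing at week 4 unless a value is filled in, however informative the week-2 score is. The named test and the intention-to-treat statement therefore do not fit together by themselves.

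What is at stake is the secondary comparisons. If the patients missing a visit differ in prognosis between the arms, the observed means differ for that reason alone. The operators know the allocation, the two treatments are visibly different, and the last visit depends on returned post, so equal loss for equal reasons cannot be taken for granted. The scores that could correct much of this are already being collected.

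**Working it through.** **Size of the expected loss.** The recruited number follows from the dropout step: 67 × 1.10 = 73.7, rounded up to 74 per arm (67 / 0.90 = 74.4 would give 75). How 67 was reached is a separate matter. Ten per cent of 74 is 7.4, so about 7 to 8 patients per arm would be absent from an unimputed test and 66 to 67 present. The article does not say to which visit the 10% refers.

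**How bias arises.** Take a standardised score (higher is worse), no true difference, correlation ρ between weeks 2 and 4, and loss before week 4 that depends only on the week-2 score. If a proportion p of an arm is lost and those lost averaged m SD at week 2, their expected week-4 mean is ρm. Because p·ρm + (1 − p)·(mean of those kept) = 0,

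mean of those kept = −[p/(1 − p)]·ρ·m.

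The bias in the arm difference is this quantity for jade minus the same quantity for control. It cancels when p and m are equal in both arms. It does not cancel when either differs.

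**Week 4, simulated** (74 per arm, SD 1, ρ = 0.65; the score-related loss in the first two rows has log-odds 1.5 per SD of the week-2 score; negative favours jade):

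| Loss, jade vs control | Cause | Bias of visit-wise difference (SD) |
|---|---|---|
| 15% vs 5% | score-related in jade, random in control | −0.117 |
| 5% vs 15% | mirror image | +0.109 |
| 10% vs 10% | score-related in jade only | −0.08 |
| 10% vs 10% | as above, half the dependence | −0.05 |
| 15% vs 5% | score-related in both | −0.07 |
| 12% vs 8% | score-related in both | −0.029 |
| 10% vs 10% | score-related in both | −0.001 |
| 15% vs 5% | random in both | 0.002 |

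Check of the first row by the formula: 0.117 = (0.15/0.85) × 0.65 × m gives m = 1.02, so the lost jade patients averaged about 1 SD worse at week 2. The third row gives 0.08 / [(0.10/0.90) × 0.65] = 1.11. These are strong selections, but consistent with the assumed slope.

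The sampling SD in the first row is 0.171, close to √(1/62.9 + 1/70.3) = 0.174 from 85% and 95% of 74. The bias is therefore 0.117/0.171 = 0.68 of a standard error. A likelihood-based repeated-measures estimate on the same data has bias −0.005 and sampling SD 0.170, so the correction costs no precision.

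**Week 24, simulated** (baseline and five follow-up visits, log-odds 1 per SD of the previous score, lost patients stay lost; the two figures are for correlations 0.5 and 0.7; only the size of the bias matters, as the arms are interchangeable):

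| Loss by week 24 | Cause | Bias, visit-wise (SD) | Two-sided error at nominal 5% | Bias using earlier visits (SD) |
|---|---|---|---|---|
| 10% / 10% | same | 0.002, 0.001 | 4.6%, 4.4% | 0.000, 0.002 |
| 5% / 15% | same | 0.048, 0.065 | 5.8%, 6.8% | 0.001, 0.004 |
| 10% / 30% | same | 0.100, 0.138 | 8.7%, 11.9% | 0.000, 0.002 |
| 10% / 10% | opposite | 0.098, 0.141 | 9.3%, 13.1% | 0.001, 0.003 |
| 5% / 15% | opposite | 0.102, 0.144 | 9.7%, 13.1% | 0.002, 0.006 |

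Opposite means that patients doing badly leave one arm and patients doing well leave the other. Loss of 30% against 20% depending on the week-12 score gave 0.15 SD (correlation 0.65). Combining opposite causes with 10% against 30% loss gave 0.21 to 0.28 SD, but that is far from the sponsor's 10% and is left out of the range quoted.

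**The case against.** **The intention-to-treat population.** A reader might infer that it will not be analysed. The article does not say so. It prescribes no restriction to patients with data at a visit, and a t-test after imputation would fit its wording. A missing-data rule is commonly left to an analysis plan or full protocol, neither of which is shown, so its absence is no finding. What stands is narrower: the method that is named works one visit at a time and by itself neither uses the other scores nor keeps everyone randomised.

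**A false non-inferiority claim.** A reader might also infer that selective loss inflates the chance of one. This is not shown. The named tests serve secondary outcomes; the main analysis is a chi-square test on week-4 remission, and 3.6 describes no non-inferiority test on a continuous score. The harmful direction needs poorly responding jade patients to leave. The only arm-specific hint in the article concerns the other arm: "Traditional moxibustion therapy produces heavy smoke with unpleasant smell". Loss there of poor responders would bias against jade, and loss for the smell alone, unrelated to response, would give about zero.

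**The size.** The largest week-4 figures combine threefold unequal loss with strong score dependence in one arm only. The previous trial lost nobody, and equal loss of the same kind gives no bias. The near-zero bias of the alternative follows from simulating loss that depends only on observed scores. All of this stands, and it is why the size is given as conditional.

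**The remedy.** A mixed model still omits patients with no post-baseline score, and for SF-36, first listed after treatment at week 4, it recovers nothing for patients lost before then. This stands as well; the model comes closer to intention-to-treat without fully reaching it.

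**Conclusion.** The point holds for the secondary continuous scores. The visit-by-visit unpaired tests discard collected information and, without imputation, cannot include every randomised patient. With loss equal in amount and cause, the consequence is negligible. With loss that differs by arm in amount or cause, bias of about 0.03 to 0.15 SD in either direction is plausible, against 0.01 SD or less when earlier scores are used. These sizes rest on assumed correlations of 0.5 to 0.7, assumed loss by arm and loss depending only on observed scores. The article gives none of these, so the actual bias is unknown.

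The main chi-square analysis would share the weakness if run without imputation: in the first week-4 scenario, with a cut-off at the mean, the observed responder rate moved about 4.7 percentage points in jade's favour. That is an illustration under a near-worst-case pattern, not evidence about the trial's error rate. The change is worth making because it is nearly free.

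**What to change.** In 3.6, replace the visit-wise tests for WOMAC pain, function and stiffness, and VAS with one repeated-measures mixed model per scale: arm, visit, arm-by-visit, baseline score and unstructured covariance. Include all randomised patients with any post-baseline score and report the arm difference with a confidence interval at each visit.

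Do the same for SF-36, stating that it recovers nothing for patients lost before week 4. Section 3.2 lists no baseline SF-36 and Table 1 is not shown, so include the baseline term if it is collected.

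If the week-4 remission rate stays the main analysis, multiply impute missing week-4 WOMAC within arm from baseline and the other visits before applying the cut-off, so that all randomised patients are counted.

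The cost is slightly more programming and reliance on a missing-at-random assumption, which should be stated. No new data, visits or patients are needed.
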